## Abstract

**Background:**

Childhood mental health (MH) problems are a major public health concern due to their high prevalence and well-documented adverse consequences, and are often under-recognized and untreated. Less effective parental emotion socialization practices play a critical role in the emergence of childhood MH problems, influencing children’s socioemotional development. Emotion-focused parenting programs, such as Tuning in to Kids^®^ (TIK), could be a promising approach to promote parents’ emotion coaching skills, enabling children to understand and regulate their emotions more effectively, while also supporting parents in managing their own emotions. Prior evidence supports TIK’s efficacy in improving children’s and parents’ MH outcomes across several countries; however, TIK’s efficacy has not yet been explored in Southern Europe. This study aims to provide a process and efficacy evaluation of TIK for parents of preschool-aged children in Portugal.

**Methods:**

This trial is a parallel two-arm randomized clinical trial, which includes both process (i.e., feasibility and acceptability) and efficacy evaluation (i.e., change in primary and secondary outcomes and moderated effects) of Tuning in to Kids^®^ in Portugal. A minimum of 152 parents/legal guardians (> 18 years old) with at least one child between 3 and 6 years old will be enrolled. Parents will be randomly assigned to the intervention group or waiting list control group (76 per condition), through blocked randomization, with allocation concealment. Participants in both conditions will complete self-report questionnaires assessing primary (parental emotion socialization) and secondary (parents and children functioning dimensions) outcomes at baseline, post-intervention, and follow-up (2 months post-intervention). Longitudinal data will be analyzed using linear mixed-effects models accounting for repeated measures within participants.

**Discussion:**

We anticipate that the Portuguese version of Tuning in to Kids^®^ will be feasible, acceptable and effective in improving parent emotion socialization (e.g., more adjusted parents’ beliefs and reactions to children’s emotions and emotion regulation skills), and parents’ and children’s psychological functioning (e.g., less parenting stress and reduced children’s emotional/behavioral difficulties). If achieved, these findings will support TIK’s use in promoting MH among families.

**Trial registration:**

The clinical trial is registered at ClinicalTrials.gov (Identifier: NCT07350083, date assigned January 13, 2026).

**Supplementary Information:**

The online version contains supplementary material available at 10.1186/s40359-026-04450-4.

## Introduction

Mental health (MH) problems in early childhood represent a growing public health concern, affecting approximately 17.6% of preschool-aged children worldwide [1]. Internalizing and externalizing problems in young children not only lead to lower academic attainment and compromised social interactions with peers but also carry long-term consequences, including poorer quality of life, impaired MH, and lower life satisfaction in adulthood [2, 3]. Although early prevention of, and intervention in, MH problems are crucial to promote optimal child development [4], access to timely and appropriate support services remains limited, leaving a considerable proportion of children without access to appropriate care, particularly in low-income families [5].

Difficulties in emotion regulation represent a transdiagnostic symptom underlying a wide range of MH problems [6] and, therefore, constitute a critical target for intervention [7]. Early parent-child interactions, particularly how parents respond to their children’s emotions and model emotional regulation, play a critical role in shaping children’s emotional competence [8]. Accordingly, interventions that enhance supportive emotion socialization parenting practices (ESPP) offer a promising venue for preventing early MH problems.

Emotion-focused parenting programs, such as Tuning in to Kids^®^ (TIK; [9]), enable children to better understand and regulate their emotions by supporting parents in managing their own emotional responses and promoting the use of emotion coaching. TIK is an evidence-based program delivered by trained facilitators in six weekly, two-hour group sessions, originally designed for parents of preschoolers [9].

Central to the program is the concept of *meta-emotion*, which refers to parents’ beliefs and behaviors regarding emotions, shaped by their past experiences and family of origin. Meta-emotion influences how parents respond to their children’s emotions and behaviors, thereby informing ESPP toward children’s emotional expression. These practices can be either supportive (*emotion coaching*) or unsupportive (*emotion dismissing*) of the children’s emotional development. Unsupportive ESPP involve parents minimizing, criticizing, or avoiding children’s emotional experiences, thus hindering the development of emotional regulation. In contrast, supportive ESPP involve parents validating children’s feelings, capitalizing emotional situations as opportunities for learning, to coach emotional understanding and regulation. Such supportive parenting practices promote children’s emotional development, strengthen parent-child relationships, and are associated with positive outcomes for parents, including greater emotional awareness [10]. The program has been shown to improve child and parent MH outcomes across several countries [11, 12].

Despite its growing evidence, TIK feasibility, acceptability and efficacy have not yet been explored in Southern European countries, namely in Portugal. This is particularly relevant considering the high prevalence of childhood MH problems reported in some of these countries (e.g., Spain) and lack of access to public MH services, especially amongst families facing socioeconomic adversity [13]. In Portugal, mental healthcare systems are often under-resourced, with long waiting lists and limited availability of specialized child MH services (e.g., [14]). Portugal has been identified as one of the Southern European countries with the highest levels of unmet healthcare needs and the widest socioeconomic disparities in access to services [15]. Socioeconomic inequalities remain a critical concern, as financial hardship and restricted access to supportive interventions place many families at heightened risk for early mental health difficulties [16]. Additional barriers to access to MH care include an insufficient supply of clinical staff and a lack of standardized referral criteria, with waiting times for pediatric psychiatric consultations averaging nearly four months in Portugal [17]. Thus, emotion-focused parenting programs, such as TIK, when delivered in the community, may offer a cost-effective strategy to address the observed alarming MH care disparities.

Equally important are the cultural differences in emotion socialization, which reinforce the need to explore the feasibility, acceptability and efficacy of emotion-focused parenting interventions in different countries. Parenting practices vary considerably across regions, with meaningful implications for children’s emotional development (e.g. [18]), . In Nordic countries, parents are more likely to value autonomy over control and tend to adopt less authoritarian parenting [19]. Such supportive practices are associated with higher children’s self-esteem and more adaptive socioemotional functioning [20].

By contrast, in Southern European countries, like Portugal and Italy, parental overprotective approaches are more frequent, characterized by higher levels of control (e.g. [21, 22]), . Although collectivist and interdependent cultures may encourage the expression of socially engaged emotions, such as empathy and guilt [23], overprotective parenting practices may also restrict opportunities for independent growth and hinder children’s development of effective emotion self-regulation [24]. In addition, despite its legal prohibition [25], harsh disciplinary strategies such as physical punishment are highly prevalent amongst Portuguese parents [26]. Adapting parenting programs to account for these cultural differences may thus help to promote greater equity in access to MH care in Southern European Countries by making such interventions broadly accessible and culturally sensitive [27].

Ensuring access to effective parenting programs is particularly relevant for disadvantaged families, where parents often face additional challenges that compromise their MH and their ability to provide adequate care [28]. At the same time, children in these families are frequently exposed to early adversity [29], associated with increased behavioral problems, which can further elicit harsher and more inconsistent parenting practices [27] and, in turn, reinforce children’s emotional and behavioral difficulties [30].

Particularly, parents’ higher sociodemographic disadvantage (e.g., lower age, education, and income) predicts lower supportive emotion socialization, as the additional stressors and limited resources of these contexts may undermine parents’ ability to cope with parenting demands and provide supportive emotional responses [31]. As a result, MH outcomes are generally poorer among these families and largely overlooked [32], which limits children’s ability to reach their full potential as adults [33]. Particularly in Portugal, where nearly 379,000 children (22.6%) are at risk of poverty and social exclusion, highlighting an urgent need for child support [13].

Parenting interventions may also provide an effective strategy to address such disadvantages. Evidence-based parenting programs can improve parenting practices and overall family functioning, as well as reduce socioemotional problems in children from disadvantaged, high-risk families (e.g., [34]. However, engagement in parenting programs is particularly challenging for families with low socioeconomic status, with prior studies showing lower attendance rates [35]. Financial costs and lower education levels are associated with poor parental attendance [36]. As a result, parents with the greatest potential to benefit from parenting programs (e.g., [37]) are often the least likely to enroll [35].

Thus, efforts to develop evidence-based, accessible, and appealing parenting programs to low-SES families are critical. Rigorous outcome evaluations, including the use of control groups and follow-up assessments, are needed to establish the short- and long-term efficacy of such interventions [38]. By fostering greater engagement amongst disadvantaged families, emotion-focused parenting programs, such as TIK, may promote supportive ESPP to improve the family environment, parental MH, and children’s emotional and behavioral difficulties. Over time, these benefits may help to reduce inequalities in MH and address critical gaps in child MH provision in Portugal.

## Objectives

Framed within the Getting To Outcomes framework [39], this trial aims to conduct a process and efficacy evaluation of TIK among parents of preschool aged children in Portugal. Regarding process evaluation, we will evaluate TIK’s (a) feasibility (e.g., adherence to the program, whether TIK is implemented as intended and enablers and barriers to TIK implementation), and (b) acceptability (e.g., satisfaction, suggestions for improvement). Regarding efficacy, we will assess whether the TIK will be able to improve parental emotion socialization (primary outcomes, e.g., parents’ reactions to children’s emotions, parental emotion regulation) and parents’ and children’s emotional and behavioral functioning (secondary outcomes, e.g., parenting stress, children’s emotional/behavioral problems). A waiting list control group will be used. We hypothesize that parents receiving TIK will (1) show improvements in parental emotion socialization and (2) report improvements in parental and children functioning, across time (i.e., from pre-intervention to follow-up), compared with parents of the waiting list control group. We will also explore whether families’ psychosocial risk moderate the TIK’s efficacy on primary and secondary outcomes.

## Methods

### Trial design

The clinical trial is registered at ClinicalTrials.gov (Identifier: NCT07350083, date assigned January 13, 2026). Ethical approval to conduct this clinical trial was obtained from the Ethics Committee of the School of Psychology and Life Sciences of Lusófona University (Ref. CEDIC-2025-10-30/CEDIC-2025-5-35). The clinical trial will be conducted in compliance with the American Psychological Association [40] guidelines and the Declaration of Helsinki [41]. The study protocol of this clinical trial follows the SPIRIT (Standard Protocol Items: Recommendations for Intervention Trials) guidelines [42] and the reporting of the RCT will followCONSORT guidelines [43].

This study is a parallel two-arm randomized controlled trial that will be conducted between December 2025 and December 2027. After completing the baseline assessment, participants will be randomly allocated to either the intervention group or the control group (allocation ratio 1:1). A wait-list group will be used to minimize threats to internal validity and because it has been considered ethically acceptable for preventive interventions [44]. Participants in the control group will receive the intervention after the follow-up assessment.

### Trial setting

This trial will be conducted in the Lisbon Metropolitan Area or Lisbon District (Portugal). Findings from a previous study showed that parents expressed a preference for sessions held in familiar community settings, such as their children’s schools or local health centers, and after work [45]. Accordingly, protocols were formally established with several community partners, and TIK sessions will be held in community settings (e.g., schools, hospitals) to facilitate participants’ enrollment and engagement.

### Participants

Eligible participants will be parents/legal guardians (hereafter referred to as “parents”) (1) with at least one child aged between 3 and 6 years old (inclusive) who lives with the parent, (2) at least 18 years old, (3) who can read, understand, and speak Portuguese, and (4) who live in the Lisbon Metropolitan Area or Lisbon District. When requested, both parents will be allowed to participate. Exclusion criteria include (1) parents’ being currently enrolled in another structured parenting program, (2) the child is already attending elementary school at the time of recruitment, (3) the child has a diagnosis of a severe Communication and/or Developmental Disorder, or (4) the child is under a child protection measure that implies that the child does not live with their parents (e.g., if the child is in foster care). Parents who have multiple children within the target age range will be instructed to respond with reference to the child for whom they experienced the most concern.

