### Study procedures

The clinical trial procedures (enrollment, intervention and assessments) are detailed in Table 1. Eligible parents who agree to participate in the project (informed consent) will complete baseline in-person questionnaires in the place where the sessions will be held. After that, they will be randomly assigned to either the intervention program condition (TIK) or the control condition. Participants in the intervention group will start TIK sessions within 1 month following the baseline assessment and will complete post-intervention and follow-up (2-month post-intervention) assessments in person. At 2-month post-intervention, a booster session will be held at the same location the sessions took place immediately after participants complete the protocol evaluation. According to the original TIK structure, this booster session is offered as an optional follow-up to consolidate skills [10]. In the present clinical trial, we chose to include this session not only to minimize parents’ attrition but also to provide participants with an additional opportunity to practice skills and discuss challenges beyond completing questionnaires. Participants in the control group will complete the same evaluation protocol at equivalent assessment time points, in the same setting as the intervention sessions, but on different days to minimize contamination between study arms. In the case of both parents participating, each will complete an evaluation protocol independently. The facilitators will complete questionnaires during the intervention (after each session) and at the end of each facilitated group assessing implementation fidelity.

**Table 1 Tab1:** Clinical trial procedure

Variables	Informant	Measures	Enrollment and screening	Baseline [T0]	Allocation	During intervention	Post-intervention [T1]	2-month Follow-up [T2]
Eligibility screening	Parent	-	*					
Informed consent	Parent	-	*					
Sociodemographic and clinical data (parent and child)	Parent	Questionnaire developed for this study		*				
	Facilitators	Questionnaire developed for this study		*				
Process evaluation								
Fidelity	Facilitators/independent observer	TIK fidelity checklist				*		
Feasibility	Parent	Questionnaire developed for this study					*	
Attendance and retention of participants in the intervention	Facilitators	Facilitators’ records				*		
Acceptability	Parent	Questionnaire developed for this study					*	
Outcome evaluation								
Primary outcomes								

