### Randomization and blinding

To ensure balanced groups throughout the enrollment period, randomization will be conducted using a permuted block procedure, with block sizes varying between 4 and 6, depending on the number of eligible parents. To ensure allocation concealment, the sequence will be generated through computer randomization software by an independent researcher not involved in participants’ enrollment or assessments. Group assignments will be further communicated to the research team, who will subsequently inform parents of their allocation via telephone. Additionally, groups’ equivalence will also be assessed regarding primary outcomes and key covariates. Considering the nature of the intervention and similarly to research evaluating TIK in other countries (e.g., [48]), this study will be an open-label trial, as neither the researchers nor the parents will be blinded to the participants’ group allocation.

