#### Efficacy evaluation

The statistical analyses will be carried out using SPSS and the R software (version 4.4.0). The level of statistical significance will be set at *p* < .05. Descriptive statistics will be computed for all study variables. Pearson/Spearman correlations will be conducted to explore associations between all the study variables at each assessment wave. Pre-test differences between the intervention and control groups will be analyzed regarding sociodemographic and health characteristics (using qui-square tests) and the primary and secondary outcomes using t-tests (for dichotomous independent variables) and one-way ANOVAs (for categorical and ordinal independent variables) to identify potential covariates.

Linear mixed-effects models accounting for repeated measures within participants will be tested to analyze TIK’s efficacy. Time 0 will be defined as the date of the pre-test assessment, time 1 will be the date of the post-test, and time 2 will be the date of the follow-up assessment. Time, group conditions (intervention (coded as 1) vs. control (coded as -1)), and the 2-way interaction time x group conditions will be included in the models as fixed effects. Moreover, for children-related outcomes (i.e., children’s emotional and behavioral functioning), the child will be treated as the primary unit of analysis and models will also include a random intercept and a random slope for time at the child level in order to account for between-child variability in baseline (at pre-test) levels of the outcome variables and between-child variability in change across time. Since both parents may participate in the study, the child-level random effects also allow one to take into account the non-independence of both parents’ reports for the same child. For parents-related outcomes (i.e., parental emotion socialization and parents’ emotional and behavioral functioning), the parent will be treated as the primary unit of analysis and models will include a random intercept and a random slope for time at the parent-level to account for between-parent variability. To account for the nesting of both parents within the same family, a random intercept at the child level will be included.

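### Both parents of a child may enrol, but allocation is by individual parent with no rule for couples, so partners can be placed in opposite arms

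*Protocol article*

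**What the plan says.** Second parents are admitted on request (Participants): "When requested, both parents will be allowed to participate". No cap or expected number of couples is given.

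The unit of allocation is described in the same way throughout:
- Abstract, Methods: "Parents will be randomly assigned to the intervention group or waiting list control group (76 per condition), through blocked randomization".
- Trial design: after baseline, "participants will be randomly allocated to either the intervention group or the control group (allocation ratio 1:1").
- Randomization and blinding: permuted blocks "with block sizes varying between 4 and 6, depending on the number of eligible parents".

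The only procedure specific to couples is in Study procedures: "In the case of both parents participating, each will complete an evaluation protocol independently". The same section has control participants assessed in the same setting as the sessions, "but on different days to minimize contamination between study arms".

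The analysis does recognise couples. For child outcomes (Efficacy evaluation), "the child will be treated as the primary unit of analysis", with a child-level random intercept and slope that also absorb the dependence between two parents' reports. For parent outcomes, a child-level random intercept stands for the family. Group is a fixed effect, coded 1 or -1. Parents with several children of eligible age "will be instructed to respond with reference to the child for whom they experienced the most concern" (Participants).

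**The concern.** Read as written, the allocation rule gives each parent a separate place in the sequence, so a couple can be split. Two consequences follow.

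First, spillover within the household. The primary outcomes are parents' reactions to and beliefs about children's emotions and their own regulation. One partner can pass such material to the other, and the control partner also rates a child who is being parented by someone in training. Any effect that crosses over raises the control mean and shrinks the contrast. Separate assessment days limit contact between arms at the site but cannot act inside a home.

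Second, the child's arm. The child is the named unit of analysis for child outcomes, yet a child with one parent in each arm carries both group codes. The random effects describe the correlation between the two reports. They neither remove spillover nor say which arm the child belongs to.

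A smaller point concerns families with two or more eligible children. Nothing requires both partners to report on the same child. If they name different ones, a child-level random effect no longer links them as one family.

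**Working it through.** **Inputs from the article.** Total N of 132 for 80% power at α = 0.05 in the primary analyses; 15% attrition; 152 to recruit, 76 per arm; blocks of 4 to 6; 1:1 allocation.

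**Assumed, because not given.** The share c of participants who enrol as couples; the fraction k of the treatment effect that reaches the control partner's reports; the within-couple correlation (ICC); a two-sided test.

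**The plan's own figure.** 132 × 1.15 = 151.8, so 152 is reproduced. The 132 comes from a simulation whose effect value and variances are not printed, so it cannot be re-derived. It is taken as given, at 66 per arm.

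**Chance that a couple is split.** Once one partner is placed in a block of size b, b - 1 places remain, of which b/2 belong to the other arm: P = (b/2)/(b - 1).
- Block of 4: 2/3.
- Block of 6: 3/5.
- Different blocks: 1/2.

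So at least half of enrolled couples are expected to be split.

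**How many couples.** With 152 participants there are 152 × c/2 couples. At c = 0.2 that is 15.2 couples, of which 7.6 (p = 1/2) to 10.1 (p = 2/3) are split. At c = 0.1 it is 7.6 couples, with 3.8 to 5.1 split.

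**Dilution and power.** A share c × p of control participants has a partner in the intervention arm, and each shows a fraction k of the effect. The contrast becomes (1 - cpk) times its value. For a test calibrated to 80%, power = Φ(2.80 × (1 - cpk) - 1.96).

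| c | k | p | cpk | Power |
|---|---|---|---|---|
| 0.10 | 0.25 | 1/2 to 2/3 | 0.013 to 0.017 | 79% |
| 0.20 | 0.50 | 1/2 to 2/3 | 0.050 to 0.067 | 76% to 74% |
| 0.20 | 1.00 | 1/2 | 0.100 | 71% |
| 0.30 | 1.00 | 1/2 | 0.150 | 66% |

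This is plain dilution. It ignores how the mixed model weights split couples, so it gives orders of magnitude only. The 80% belongs to the primary, parent-reported outcomes.

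**Price of allocating families.** The design effect is about 1 + c × ICC. At c = 0.2:
- ICC 0.1: 132 × 1.02 = 134.6, so 135.
- ICC 0.5: 132 × 1.10 = 145.2, so 146.

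By the article's own inflation (× 1.15) that means recruiting 156 to 168; dividing by 0.85 gives 159 to 172. If N stays at 132, power is 79% to 76%.

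**The case against.** The article never says that partners are randomised separately. It is a condensed text, and a full protocol could hold a rule for couples. The modelling language about two parents nested in one family is compatible with joint allocation. That limits the point to what the stated rule permits. It does not remove it, because the parent is named as the unit several times, blocks are counted in parents, and no exception appears where couples are discussed.

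Four stronger readings are tempting and are not supported:

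- **That the control arm is contaminated.** The size depends on the couple share and the spillover, neither of which is given. Second parents join only on request. If few do so and little crosses over, the loss is about one percentage point of power.
- **That the child-outcome model needs one arm per child and so fails.** A mixed model can be fitted when group differs between two reports on one child. What suffers is the meaning of the contrast.
- **That child outcomes fall from 80% to 66-71% power.** The 80% is stated for the primary analyses, and child outcomes are secondary with no stated power. The 66-71% also assumes that an untrained parent's reports show the whole effect.
- **That partners choose index children separately.** The text says only that they complete questionnaires independently. Different choices are possible, but only in families with two or more eligible children.

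Nor do the separate assessment days lose their purpose: they still work for everyone outside a split couple.

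**Conclusion.** The concern holds in conditional form. The allocation rule as written lets partners fall into opposite arms, and would be expected to split at least half of the couples who enrol. In those families both the parental and the child contrasts can be diluted, and the child has no single arm.

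The size is uncertain. Power of 79%, 74-76% or 66-71% in place of 80% spans mild to severe assumptions, all of them outside the document; for child outcomes these figures only illustrate.

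The case for change rests on bias and on a defined arm more than on power. At 20% in couples, family allocation without a larger sample also costs one to four points. But that loss can be made good with more families, whereas no analysis restores an unexposed control report once a couple has been split.

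**What to change.** State in Randomization and blinding that parents of the same child are allocated as one unit, with one allocation per family and blocks counted in families. For families with more than one eligible child, fix one index child at baseline and have both parents report on that child at every assessment. Use family ID, not the reported child, as the nesting level that links partners.

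Families already randomised keep their allocation. Add a sensitivity analysis that excludes split couples; each exclusion removes one participant from each arm.

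Costs: a slight imbalance in parents per arm; a design effect of about 1 + c × ICC, to be reflected by restating the power with an assumed couple share and ICC; and an ethics amendment, which the article requires before any modification is implemented.

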## Measures

### Sociodemographic measures

A questionnaire specifically developed for this study will collect sociodemographic and health-related data at baseline, referring to the parents (i.e., sex, education, nationality, ethnicity, professional status, marital status, if currently in a marital relationship with the other child’s parent, monthly family income, receipt of financial support from public entities or others, perceived sufficiency of household income, receipt of support from social services, household size, history of MH problems) and the child (i.e., sex, age, and existence of mental, physical and/or developmental problem).

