### Data management

Data management of this clinical trial will follow Lusófona University’s data protection policies and the General Data Protection Regulation (GDPR - UE, 2016/679). Research assistants will be responsible for data collection and data entry. Data from paper questionnaires will be entered on REDCap. By including range checks, field validation, mandatory fields, logic rules, and indicators of missing values, among other features, REDCap allows enhancing data quality in terms of its accuracy, completeness, and reliability. To maximize data accuracy, two independent research assistants will enter the same paper questionnaires into REDCap, which will compare the two entries and signal any discrepancy. Paper questionnaires will be kept at Lusófona University (access restricted), and any identifying data will be removed. Each participant will receive an ID code that would allow pairing data across assessment points. Pseudonymized data will be stored at Lusófona University server, after being encrypted and accessed by password, as well as signed consent forms. Only research assistants and project coordinators will have access to the data. Participants will have the right to access, change, or delete their own data at any time, as well as to remove their consent for participation, with no need for explanations. Data will be maintained for the time strictly necessary for achieving this project’s aims.

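### Two partners may each rate a different child, but the mixed models assume one child per couple and use the child as the family identifier

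*Protocol article*

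**What the plan says.** Three sections of the protocol article bear on this.

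- **Participants.** On enrolment of couples: "When requested, both parents will be allowed to participate". Parents with more than one child in the age range "will be instructed to respond with reference to the child for whom they experienced the most concern". The criterion is the parent's own concern. Nothing is said about partners agreeing on a child.
- **Study procedures.** "In the case of both parents participating, each will complete an evaluation protocol independently".
- **Efficacy evaluation.** For child outcomes the child is the unit, with a random intercept and a random time slope at child level, and "the child-level random effects also allow one to take into account the non-independence of both parents’ reports for the same child". For parent outcomes, which include all the primary outcomes, the parent is the unit. The family is handled thus: "To account for the nesting of both parents within the same family, a random intercept at the child level will be included".

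The only linkage described under Data management is by participant: "Each participant will receive an ID code that would allow pairing data across assessment points". Participants are the parents. No child code or family code is mentioned.

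**The concern.** The data-collection rules and the models do not fit together for one kind of family. The first two sections allow a mother and father with two preschoolers to report on different children. The analysis section treats that as impossible: it speaks of both reports as concerning one child, and it lets the child stand in for the family.

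At stake are two things. For SDQ-P and ERC, the child-level trajectory could be built from reports on two different children. For the parent outcomes, the within-family dependence that the plan sets out to model could be missing for those couples. This is a conflict between stated rules, not a detail that an article would normally leave to a longer document.

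**Working it through.** The plan gives no figure on this point, so the check sets the rules side by side and follows them through each type of family.

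**1. Family types**

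- *One parent enrolled.* There is no partner report, so the conflict does not arise.
- *Both enrolled, one eligible child.* Both reports concern that child, and the child code and family code coincide. The models are specified as intended.
- *Both enrolled, two or more eligible children, same child named.* As above.
- *Both enrolled, two or more eligible children, different children named.* The stated rules permit this and the models do not provide for it.

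**2. What the models do in the last case**

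Parent outcomes. Write the planned model for parent p, with rated child c, at time t as

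Y = fixed part + u(c) + a(p) + b(p)·t + error.

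The covariance it allows between two partners is Var(u) if they share c, and 0 if they do not.

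- *Each partner carries the code of the child actually rated:* the two codes differ and the modelled covariance is 0. The family link is lost. Each such child then has only one parent attached, so for that couple u(c) cannot be told apart from a(p).
- *One code is forced on the couple:* the family link is kept, but the code no longer denotes a child.

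Child outcomes. Write the planned model as

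Y = fixed part + u(c) + v(c)·t + error.

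Two reports on the same child share u(c) and v(c).

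- *Separate codes:* the siblings enter as unrelated children.
- *One code:* two children are forced to share one intercept and one slope, and the real difference between them goes into the error term. The term meant to capture "between-child variability in change across time" then describes neither child.

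No coding choice repairs both sets of models, because one identifier is asked to do two jobs.

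**3. How often partners might disagree (assumed inputs)**

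Take a couple with two eligible children. Let each parent's difference in concern between the siblings be normal with mean 0, with correlation ρ between the parents. The parents name different children when the two differences have opposite signs:

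P(different) = arccos(ρ)/π.

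- ρ = 0.3: 1.266/3.142 = 0.40
- ρ = 0.5: 1.047/3.142 = 0.33
- ρ = 0.7: 0.795/3.142 = 0.25

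So among every 10 such couples, roughly 2.5 to 4 would name different children. The range for ρ is an assumption; the article gives no value.

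**4. Reach in the whole trial**

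Affected couples = (couples with both parents enrolled) × (share with two or more eligible children) × (0.25 to 0.40). The article gives neither of the first two terms, so no trial-wide number can be stated.

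**5. Which outcomes**

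SDQ-P and ERC are ratings of a particular child, so they are hit directly. The primary outcomes (CCNES, PBACE, IM-P, DERS-SF) are scored as properties of the parent and are touched mainly through the lost family intercept. Because that term is an intercept, it cancels from a parent's change over time when all waves are complete. The group-by-time test on the primary outcomes should therefore move little.

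**The case against.** The strongest reply is that the intention is clear. The analysis section says the child-level intercept is there to represent the family and speaks of one child for both parents, so the authors evidently have one index child per family in mind. In families with a single eligible child the model is right. Couples join only on request, few may have two preschoolers, and the outcomes most affected are secondary. All of this stands and limits the size of the point. It does not remove it, because the selection rule as written does not deliver the single child that the models need.

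A reader might go further and draw three stronger conclusions. The article does not support them.

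- *That parents choose again at post-intervention and follow-up, so that the rated child changes between waves.* The article does not say the instruction is repeated. It uses the past tense, collects the child's descriptors once at baseline, and fits a child-level time slope. All three point to one child throughout. A change of child is only a possibility left open by silence.
- *That such changes would differ by arm and pull the effect toward zero.* This needs the re-selection just described, and also little or no benefit to the sibling. The article supports neither, so no figure should be attached to it.
- *That ineligible children would be rated.* The exclusion criteria are written about the child, directly before the sentence on choosing one, and eligibility is checked by telephone before consent and baseline. The natural reading is that the rated child is the one who was screened.

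**Conclusion.** The point holds in a limited form. Following the stated rules, partners with two or more eligible preschoolers can rate different children, and for those couples the planned models either lose the family link or merge two children into one random effect. Families with one enrolled parent or one eligible child are unaffected.

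About 25% to 40% of the exposed couples would be discordant if inter-parent agreement lies in the assumed range of 0.3 to 0.7. How many couples are exposed is unknown. The consequence is mainly for the secondary outcomes SDQ-P and ERC, with a smaller effect on the primary-outcome models through family clustering. It does not threaten the trial's main conclusion, but it is worth correcting because the correction is nearly free and a mismatch is hard to detect afterwards without a recorded child code.

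**What to change.** Replace the sentence on choosing the child with wording such as: *One index child per family is fixed before baseline, among the children who meet all eligibility criteria. It is the child of most concern; if both parents take part, they agree on one child.*

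Then:

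- Record a child code and a family code in REDCap.
- As a safeguard, name the index child on the forms at T0, T1 and T2 for both parents.
- In the parent-outcome models, put the random intercept on the family code instead of the child code. Keep the child code for the SDQ-P and ERC models.
- For families already enrolled, confirm which child each parent rated at baseline and carry that child forward. Where partners named different children, keep separate child codes joined by the family code.

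The cost is one or two sentences, two REDCap fields and one changed grouping variable, with no extra visits or staff. Recruitment is expected to run to 28 February 2027, so families still to be enrolled would be covered from baseline.
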